## Abstract

**Background:**

Low- and middle-income countries face difficulties in providing adequate health care. One of the reasons is a shortage of qualified health workers. Diagnostic decision support systems are designed to aid clinicians in their work and have the potential to mitigate pressure on health care systems.

**Objective:**

The Artificial Intelligence–Based Assessment of Health Symptoms in Tanzania (AFYA) study will evaluate the potential of an English-language artificial intelligence–based prototype diagnostic decision support system for mid-level health care practitioners in a low- or middle-income setting.

**Methods:**

This is an observational, prospective clinical study conducted in a busy Tanzanian district hospital. In addition to usual care visits, study participants will consult a mid-level health care practitioner, who will use a prototype diagnostic decision support system, and a study physician. The accuracy and comprehensiveness of the differential diagnosis provided by the diagnostic decision support system will be evaluated against a gold-standard differential diagnosis provided by an expert panel.

**Results:**

Patient recruitment started in October 2021. Participants were recruited directly in the waiting room of the outpatient clinic at the hospital. Data collection will conclude in May 2022. Data analysis is planned to be finished by the end of June 2022. The results will be published in a peer-reviewed journal.

**Conclusions:**

Most diagnostic decision support systems have been developed and evaluated in high-income countries, but there is great potential for these systems to improve the delivery of health care in low- and middle-income countries. The findings of this real-patient study will provide insights based on the performance and usability of a prototype diagnostic decision support system in low- or middle-income countries.

**Trial Registration:**

ClinicalTrials.gov NCT04958577; http://clinicaltrials.gov/ct2/show/NCT04958577

**International Registered Report Identifier (IRRID):**

DERR1-10.2196/34298

## Introduction

### Background

Basic health care is insufficient for an estimated 4 billion people worldwide due to a global shortage of up to 7.2 million health care workers, which is expected to increase to a shortage of 12.9 million workers by 2035 [1]. The shortages in sub-Saharan Africa will be among the most profound because of a scarcity of medical schools in the region and an overall lack of training [1]. Additionally, poor clinical knowledge is a concern in regards to the level of care given worldwide [2]. A World Bank report found that 50% of rural health care workers were unable to diagnose 5 common conditions affecting patients in Tanzania [3]. Clinical deficiencies lead to a high number of excess deaths in low- and middle-income countries (LMICs) that would be prevented by the provision of higher-quality health care [4]. Clinical decision support systems (CDSSs), such as diagnostic decision support systems (DDSSs) can help to mitigate these problems. A few studies have investigated whether mobile phone–based CDSSs have enabled health care workers to provide better treatment, but thus far evidence is inconclusive [5]. It is therefore important to undertake further research on this topic in order to assess the potential role of mobile device–based CDSSs.

CDSSs are often implemented in real clinical settings and used by health care providers (HCPs) to aid decision-making at the point of care or for a specific care situation. The usefulness of CDSSs can be measured according to many different types of outcomes, such as clinical and health care processes or user workload and efficiency [6]. There is a great opportunity for CDSSs to improve patient outcomes with proper adherence; an example of these improved outcomes can be seen in one study, in which the final process composite score and patient satisfaction were higher in the patient group that used the CDSS compared to the group that did not [7]. One great challenge to CDSS and DDSS adoption and their clinical benefits is system usability. These systems must be practical and useful in a manner that supports their ongoing use by HCPs; this is a consistent challenge with almost all CDSSs [8,9].

### DDSS Evidence Base

A number of studies have explored the use of DDSSs in high-income countries (HIC) [10], where the rate of diagnostic error in clinical medicine is estimated to be as high as 15% to 50% [11]. A published systematic review of available DDSSs showed that they can provide accurate diagnostic suggestions [10], with a pooled accurate diagnosis retrieval rate of 70%. That review also presented preliminary evidence that small but significant improvements in physician diagnostic accuracy accompanied DDSS use. It has also been recognized, however, that many DDSSs provide long lists of suggested conditions, which might increase clinician uncertainty. Another barrier to DDSS uptake is the additional time required for their use. A systematic review by Riches et al [10] suggested that junior members of clinical teams, or those with less medical experience, input more data and were therefore more likely to benefit from the use of DDSSs. This is indicative of the potential of DDSSs in LMICs, where diagnoses are often made by HCPs with less formal medical training than medical doctors [3]. Overall, the review concluded that differential diagnosis generators have the potential to improve diagnostic practice among clinicians; however, the literature that they reviewed also revealed many caveats that must be considered in the application of these systems and their further development. For example, it was reported that accurate diagnosis retrieval alone does not predict the uptake or effectiveness of differential diagnosis generators in clinical settings, as there are other relevant characteristics that can influence uptake and effectiveness, including the specificity of the list of diagnoses, the time required to use the system, its availability and access, and its cost-effectiveness [10,12,13].

There have been fewer studies of DDSSs in LMIC settings. Although addressing diagnostic error is complex, suggested approaches and solutions include training in diagnostic techniques for clinicians and the use of electronic diagnostic aids, such as DDSSs, to augment the diagnostic abilities of doctors [10]. In a study conducted in Mexico that looked at a range of clinical patterns, a DDSS was shown to improve the diagnostic accuracy of family medicine residents for both rare and common illnesses alike; they achieved an accuracy of 82.4% (SD 8.5%) with the DDSS and 74.1% (SD 9.4%) without the DDSS [14].

DDSSs may have a role in upskilling health workers and in supporting doctors’ decision-making in the medium term. However, health-related artificial intelligence solutions developed in and for high-resource settings should not simply be used in an LMIC setting without adequate clinical investigation. Due to their development in settings with different health care structures and health care worker education levels, and their development on a base of medical data biased toward these settings, one cannot simply extrapolate data from HICs to LMICs. Instead, it is important to carry out clinical evaluations that specifically demonstrate the safety and performance of the technology for individual LMIC settings and its underlying medical reasoning before its use can be extended to new LMIC locations and use cases.

### Mid-level Health Care Workers

This study will be conducted in a district hospital in Tanzania, where the main entry point for patients into the health care system is primary care [15]. Primary care is delivered in an outpatient setting that includes dispensaries, health centers, and district hospitals [16]. In Tanzania, the health care staff shortage is severe; staffing is estimated to be 52% of the actual need [17]. Mid-level health care workers compensate for the insufficiency of qualified medical doctors by carrying out some aspects of the roles of doctors. Mid-level health care workers are a group predominantly found in LMICs [18]. They are defined as health care workers who undergo shorter training than physicians, but who nonetheless perform some roles generally considered part of a physician’s responsibilities [18]. In Tanzania, mid-level health care workers include clinical officers (COs) and assistant medical officers (AMOs) [19].

After graduating from secondary school, COs receive 3 years of practical and theoretical training. A CO’s responsibility is diagnosing and treating common conditions and performing minor surgeries. After gaining 3 years of practical experience, a CO can undergo a further 2 years of training to become an AMO. The position of an AMO involves a wider scope of medical practice; they can perform surgeries such as appendectomies and cesarean sections. Additionally, AMOs can act in leadership roles in medical facilities, especially in rural areas [19]. The prototype DDSS in our study will be used by COs. If there is no CO available for the patient consultation, then it will be used by an AMO. By evaluating the use of the prototype DDSS by mid-level HCPs, we aim to assess its potential to improve the performance of HCPs who have received less medical training than fully-qualified medical doctors.

### Objective and Hypotheses

This study is part 2 of the AFYA (Artificial Intelligence-Based Assessment of Health Symptoms in Tanzania) study series [20]. The current study will explore the potential of the prototype DDSS to empower HCPs in LMICs. The objective is to measure to what degree the prototype DDSS can enhance the diagnostic accuracy of mid-level HCPs. This will be done by comparing, in an observational study setting, the diagnostic accuracy of HCPs who use the study tool to HCPs performing usual care, henceforth referred to as usual HCP, and by comparing the accuracy of diagnoses submitted before and after input from the DDSS. Since impracticality is a common barrier to CDSS adoption [8,9], we will also collect qualitative data on the usability, usefulness, and acceptance of the prototype DDSS. These measurements will provide insights on the appropriateness of the prototype DDSS interface.

There are two study hypotheses: (1) a “chatbot”-based DDSS, which is similar to a symptom assessment app (SAA) as it asks a series of questions about the patient’s symptoms using a sequential “question flow,” is an appropriate interface for improving the accuracy of decision-making by mid-level HCPs in sub-Saharan Africa; and (2) the diagnostic accuracy of mid-level HCPs will be improved by the use of a “question flow” DDSS based on a chatbot.

## Methods

This study is the second of 2 studies in the AFYA study series, and is a prospective, 2-arm observational study conducted at Mbagala Rangi Tatu Hospital, Dar es Salaam, Tanzania. The first study was a general, prospective, observational assessment of a symptom assessment platform named “Ada” (Ada Health GmbH) that is used directly by patients. That study used the same clinical setting as the present study and a separate clinical study protocol that has been described previously [20].

The development of the trial protocol was conducted in accordance with the current Standard Protocol Items: Recommendations for Interventional Trials (SPIRIT) guidelines (Multimedia Appendix 1) [21].

### The Ada Prototype DDSS Specifications and Rationale of Use

The prototype DDSS evaluated in this study is being developed through an iterative user-centered design approach [22]. It has been modified from a CE (Conformité Européenne)-marked SAA [23] that was developed to provide laypeople the opportunity to determine what might be causing their health problems.

As part of the iterative user-centered process, we have explored different tools reported in various past studies, including by a study conducted in a British primary care waiting room that investigated the usability, acceptability, and utility of an SAA [24], a study conducted in a German emergency department that assessed urgent-care advice provided by an SAA [25], and another study in a German emergency department that gathered patients’ relevant symptoms and presented them to their physicians [26]. Additionally, Ada Health GmbH has developed a prototype HIC DDSS that uses the same underlying Ada medical intelligence platform but does not utilize a chatbot interface; it allows HCPs to update symptoms in real time without relying on a question flow. It also allows HCP-level clinical symptom and test-finding information to be entered. We have conducted careful formative usability research in collaboration with academic expert centers; this has also contributed to the iterative user-centered design process [27]. This HIC HCP-facing DDSS has shown potential for assisting early diagnosis of rare diseases [28], with the potential for economic benefits to health care systems [29] and potentially longer-term transformational benefits for rare disease management [30]. In cooperation with usability researchers and user interface designers, we have incorporated the findings from these studies into the further development of a DDSS prototype.

We determined that the HIC prototype DDSS explored in past studies [27-29] may not be optimal for low-resource settings, as it is less suited to the mobile phone interface and relies on physician training for effective use. We therefore explored the development of a simpler chat-based DDSS for lower-income settings, where the question-flow prompting of the HCP could provide clinical histories and diagnostic benefits.

The prototype DDSS used in this study was created for use by LMIC health care workers, initially in an observational clinical study setting, to investigate the hypotheses of this study and to further understand the DDSS requirements of mid-level HCPs. The “chatbot” prototype DDSS interface asks the HCP to enter the patient’s age and their presenting complaint, followed by basic health information, such as the presence or absence of diabetes and hypertension, smoking, and pregnancy status (if relevant). It then asks a series of questions about the patient’s symptoms, with the optimal question asked at each point of the question flow so as to determine the most relevant information in a manner that is dynamically updated based on each answer provided by the patient. In this study, the chatbot is used on a handheld tablet, but it can be used in real world settings on any device with an internet connection, including smartphones, desktops, and laptops. The prototype DDSS will use the English language. This was decided after consultation with the HCPs involved in the study. The user interface of the study tool can be seen in Figure 1.

**Figure 1 figure1:**
[figure not shown]
Screenshots showing the user interface of the tool in this study.

Dynamic questioning is delivered by the system’s underlying medical intelligence using a medical knowledge base built by medical doctors to define a Bayesian network. This Bayesian network allows approximate inference to be carried out. Based on a user’s answers, the system dynamically decides which questions to ask next in order to generate a list of potential conditions [24]. In this study, the Ada assessment was used to help mid-level HCPs gain relevant insights into the patient’s condition during their consultation by asking questions about the patient’s symptoms in an order determined by the system’s underlying reasoning engine. After the assessment, the HCP received a list of possible “condition suggestions” determined by the reasoning engine based on the patient’s presenting complaint and their symptoms. Along with these condition suggestions, the HCP was provided with additional information regarding the presentation of the disease, so that the HCP was able to make a more informed diagnosis.

The accuracy and comprehensiveness of the Ada platform has been validated in several studies of the Ada SAA [31-33]. In 2020, the Ada SAA, which uses the same medical reasoning as the prototype DDSS, was shown to be market leading in the accuracy of its condition suggestions and urgency advice compared to 7 other SAAs, and it had condition suggestions and safety performance comparable to United Kingdom general medical practitioners [31]. In a more recent study comparing 12 tools, the Ada SAA had the highest diagnostic accuracy at the first diagnosis (72%), while the next best SAAs achieved accuracies of 68% and 59.5%, respectively. Overall, the mean accuracy of all 12 SAAs was 37.7% [33]. When evaluating urgency advice, the Ada SAA was rated third best, with an accuracy of disposition of 64% (accuracy was 90% and 66.7%, respectively, for the first- and second-best SAAs), while the mean accuracy achieved by all SAAs was 57.7% [33].

### Study Optimization Phase

Before continuing on to the pilot study, there will be a feasibility and process optimization phase in which 15 patients will be recruited. This phase is for the optimization of general study procedures, patient tracking, and information recording in the busy clinical environment. In this phase, we will also be able to determine if staff training has been adequate and if the assessment is properly optimized for use by health care workers. Any deficiencies in the study process or staff training will be identified and a period of up to 2 weeks will be allowed for the rectification of any identified issues. Usual care for the patients will not change, and the data from these patients will not be included in the study analysis. After the optimization phase, at least 50 patients will be recruited for the pilot study.

### Patient Population and Eligibility Criteria

In this study, children, adolescents, and adults who arrive at the study site will be assessed for eligibility. The study site will be a busy district hospital waiting room at Mbagala Rangi Tatu Hospital in Dar es Salaam, Tanzania. Any person who enters the clinic and is willing or able to provide consent will be included, except for (1) patients who are not capable of completing a health assessment (eg, due to mental impairment, inebriation, or another incapacity) (2) patients with severe injury or illness that requires immediate treatment, or (3) patients with traumatic injury. Data from patients dropping out of the study or deviating from the protocol will be excluded from analysis.

In order to ensure that the study has a sample of patients with a comprehensive spectrum of symptom constellations and conditions, inclusion of patients will be monitored throughout the study; doing so will ensure that this pilot study does not just provide detailed testing for the most commonly presenting patient scenarios, but also provides testing for the performance of the prototype DDSS for a broad range of medical conditions. There will be a target of enrolling between 2 to 5 patients for conditions related to (1) abdominal pain or gastrointestinal issues, (2) the lower respiratory system, (3) the upper respiratory system, (4) mental health, (5) vision, (6) orthopedic issues, (7) the cardiovascular system, (8) the genitourinary system, (9) the neurological system, (10) the skin, (11) obstetrics and gynecology, and (12) the ear, nose, and throat. We plan to include at least one adult and one child in each category, where reasonable, and once a total of 5 patients have been enrolled for a given category, no further patients will be included. In cases in which the presenting complaint does not match the condition category with which the patient is ultimately diagnosed, the physician’s diagnosis will be aggregated on a dashboard adapted to optimize recruitment according to the categories listed above.

The maximum of 5 patients in one condition category is only an aim, but one that should be readily attainable. The study trackers hired for this study, that is, the workers who will recruit the patients, have CO and nurse midwife education and training, meaning that they are able, to a great extent, to determine these classifications.

### Interventions

This is an observational, prospective study. There will be no experimental or control interventions.

### Description of Study Visits and Assessment Schedule

The patient's journey in the study will consist of 3 stages (Figure 2 shows an overview).

**Figure 2 figure2:**
[figure not shown]
The patient journey in the study. Step 1: using the study tool, a differential diagnosis list is created by the study health care practitioner (clinical officer or assistant medical officer). Step 2: using a structured electronic case report form (eCRF), the patient consults with the usual health care practitioner for the determination of a diagnosis. Step 3: using a structured eCRF, the patient consults with a study physician to confirm the findings in step 2 with higher objectivity and a gold standard diagnosis. DDL: differential diagnosis list; pDDSS: prototype diagnostic decision support system.

### Patient Presenting to the Clinic (Recruitment Process)

For the recruitment process, the study staff will work in close cooperation with the hospital staff in order to identify potentially eligible patients in the waiting room. Patients assessed as potentially eligible will be approached by the study staff. The study staff will provide them with detailed information about the study and obtain written informed consent if the patients decide to enroll in the study. In addition to their parent’s or caretaker’s consent, children aged between 9 and 18 years will be requested to sign an assent form themselves. Enrolled patients will receive a unique study ID that is not part of the usual health care record and will be allocated alternately to the 2 study arms.

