### Endpoints

#### Primary Endpoints

The first endpoint will be the condition suggestion accuracy and comprehensiveness of the prototype DDSS, evaluated against the gold standard differential diagnosis determined by the review panel, reported in the context of the accuracy of the usual HCP. The second endpoint will be the study HCP’s condition suggestion accuracy and comprehensiveness, which will be compared between arm 1 (in which the HCPs determine their own list of condition suggestions before seeing the prototype DDSS’s condition suggestions, then create a final ranked list of condition suggestions) and arm 2 (in which they see the prototype DDSS’s condition suggestions before determining their list of overall ranked condition suggestions). The third endpoint will be a comparison of the study HCP's condition suggestion accuracy and comprehensiveness in arm 1 in the preliminary and final DDLs.

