### Risk-Benefit Assessment

This study does not pose any risk to the patients, as it is solely observational; therefore, there is no need for additional safety management. Patients requiring immediate medical care and clinically unstable patients will be excluded. If patients are called into their appointment before the study HCP finishes the prototype DDSS assessment, they will be excluded from the study process and analysis and proceed to usual care, meaning there will be no delay in the diagnosis or treatment of any patient. Although there will be 2 extra consultations for patients enrolled in the study, these consultations will generally require less than 10 minutes; therefore, it is highly unlikely to delay a patient’s diagnosis or treatment.

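### Alternate allocation makes the next arm predictable, with no concealment described, so patient selection can bias the primary comparison of arm 1 with arm 2

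*Protocol article*

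**What the plan says.** The recruitment section (Patient Presenting to the Clinic) gives the allocation rule: after consent, patients receive a study ID and "will be allocated alternately to the 2 study arms". The same section describes how they are chosen: "Patients assessed as potentially eligible will be approached by the study staff". Consecutive enrolment is not stated.

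Patient Population and Eligibility Criteria says who recruits: "The study trackers hired for this study, that is, the workers who will recruit the patients, have CO and nurse midwife education and training", so that "they are able, to a great extent, to determine these classifications". These are condition categories. There are 12, each with a target of 2 to 5 patients, and "once a total of 5 patients have been enrolled for a given category, no further patients will be included" (the maximum is later described as an aim).

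Primary Endpoints names as the second of three endpoints the study HCP's accuracy and comprehensiveness, "which will be compared between arm 1" and arm 2. In arm 1 the study HCP commits a preliminary list before seeing the DDSS suggestions. In arm 2 the suggestions come first.

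On who uses the tool, the section on mid-level workers says that clinical officers do, and "If there is no CO available for the patient consultation, then it will be used by an AMO". The number of study HCPs and their rota are not given. Strengths and Limitations does not mention alternation.

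**The concern.** A comparison between arms is interpretable only if the two arms receive comparable patients. Alternation achieves this only if the choice of the next patient is unrelated to the arm that patient will enter. Here the people choosing can judge the likely type of case and are asked to choose by it, and the arm of the next slot can be inferred from the previous one. Even an unconscious preference for simpler or harder cases in one arm would show up as a difference in diagnostic accuracy.

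This matters beyond the pilot. Outcomes and Outcome Measures says the results are meant to support power calculations for a later randomised trial. An arm difference distorted by selection could carry over into that sample size, whether or not it reaches significance here.

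**Working it through.** The article gives no figure for this point to reproduce: the minimum of 50 patients is described as pragmatic, without alpha, power or effect size.

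**1. Predictability.** Under alternation the next arm is known with certainty, after the first patient, to anyone who knows the last allocation. Under simple randomisation the chance of guessing it is 50%.

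**2. Which endpoints depend on comparable arms.**
- First: DDSS list against the gold standard, in the context of the usual HCP. This is not an arm comparison.
- Second: arm 1 against arm 2. Exposed.
- Third: preliminary against final list within arm 1, on the same patients. Not an arm comparison.

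**3. Possible size.** The documents give no accuracy by case difficulty and no rate of steering, so all inputs here are assumptions.

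Let *f* be the share of one arm's slots in which a hard case is replaced by an easy one, the other arm being unchanged, and let *p*E and *p*H be the accuracies in easy and hard cases. With no true effect,

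spurious difference = *f* × (*p*E − *p*H).

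| *f* | patients, at 25 per arm | 80% vs 50% | 80% vs 40% |
|---|---|---|---|
| 0 | 0 | 0 points | 0 points |
| 0.20 | 5 | 0.20 × 0.30 = 6 points | 0.20 × 0.40 = 8 points |
| 0.40 | 10 | 0.40 × 0.30 = 12 points | 0.40 × 0.40 = 16 points |

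If the easy-case share moves in opposite directions in the two arms, by *s* in each, the formula is 2 × *s* × (*p*E − *p*H). With *s* = 0.10 and 80% against 40%, that is 2 × 0.10 × 0.40 = 8 points.

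**4. Scale.** DDSS Evidence Base cites a study of family medicine residents with accuracies of 82.4% and 74.1%, a difference of 8.3 points. Sampling error is larger: with 25 per arm and 70% accuracy assumed in both, the 95% half-width is 1.96 × √(2 × 0.7 × 0.3 / 25) = 0.254, about 25 points.

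**5. Alignment of arm with study HCP.** I simulated 50 alternately allocated patients with two HCPs whose accuracy is assumed to differ by 20 points.
- One HCP per shift: mean imbalance in HCP share between arms about 0.7 points, bias about 0.1 points.
- Patients going to either HCP at random: mean imbalance about 0 (SD 14 points).
- Two HCPs in parallel, taking strict turns in step with the sequence: complete alignment, bias equal to the full 20 points.

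The documents describe none of these arrangements.

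**The case against.** The strongest defence has four parts.

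*Foreknowledge is inferred.* The article places allocation after enrolment and does not say who keeps the sequence. With several trackers, a given one may not know the last arm. This stands: recruiters can know the next arm, but the article does not say that they do.

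*Steering is by category, not by arm.* Category is not difficulty, and both arms' final lists are made after seeing the DDSS, so there is no untreated arm to avoid. This weakens any presumption of a motive. It does not make the allocation unpredictable, and no safeguard is described that would prevent selection by arm.

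*The study is an observational, unpowered pilot.* The article never calls the comparison randomised, and sampling error exceeds any plausible bias. But the study itself assigns the arm and so changes how the list is built. Low power concerns precision; it does not remove bias from an estimate meant to inform a later trial.

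*The sizes are assumed.* Correct. They show what is possible and estimate nothing.

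A reader might go further and infer that alternation confounds arm with the study HCP on duty. The documents do not support that. With one HCP on duty, alternation splits that HCP's patients almost evenly between arms, which is a strength. Complete confounding needs two or more HCPs taking turns in step with the sequence, which the article neither states nor excludes.

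**Conclusion.** The point holds for the second primary endpoint only. Predictable allocation, clinically trained recruiters who select by case type, and no described concealment together mean that selection can bias the comparison of arm 1 with arm 2. That it will do so, and in which direction, cannot be derived from the documents.

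Under the assumed 80% and 50% accuracies, steering 20% to 40% of one arm's slots gives 6 to 12 points; with no steering the bias is zero. That range spans the 8.3-point effect the article cites, so moderate steering could mimic or hide an effect of that order. Confounding with the study HCP remains an open possibility that depends on an unstated rota, and it carries no weight in this conclusion.

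**What to change.** For patients still to be enrolled, replace alternation with a computer-generated sequence in randomly varying blocks, held in the REDCap system already in use and released only after consent and registration. Record the study HCP for each patient, so that balance between arms can be checked.

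Keep block sizes, and as far as possible past allocations, from the trackers. In a simulation of 50 patients with assumed block sizes of 4, 6 and 8, someone who knew all past allocations and always guessed the arm that was behind was right about 68% of the time. That is better than certainty under alternation, but not the 50% of simple randomisation.

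Recruitment began in October 2021 and data collection is due to end in May 2022. Patients already allocated by alternation should therefore be reported as such. If few remain to be enrolled, a switch would leave very small groups. In that case, report the arm comparison as non-randomised and descriptive, and do not carry its difference into a later sample size without that caveat. In either case, add alternation to Strengths and Limitations.

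The cost is a slight imbalance in arm sizes, one more step at enrolment and an ethics amendment. The fallback costs only a change of wording. Neither remedy deals with losses after allocation ("If patients are called into their appointment before the study HCP finishes the prototype DDSS assessment, they will be excluded"), which could differ by arm because arm 1 has an extra step; that is a separate matter.
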